### Statistical analysis

Data will be analysed using the SPSS statistical software package and an intention-to-treat approach will be applied. Analyses will include standard descriptive statistics, Student's t tests, correlation and regression, and two-way (group × time) repeated measures ANOVA (or ANCOVA as appropriate) to examine differences between groups over time. All tests will be two-tailed and an alpha level of 0.05 will be applied as the criterion for statistical significance.

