### Calculation of sample size

Data from our research team in prostate cancer patients indicates that the standard deviation (SD) for change in our primary outcome which is the physical function subscale of the Medical Outcomes Study Short-Form 36 (SF-36) equates to ~12 points following a 3-month intervention. Given the health status of men in the proposed study we anticipate that our 3-month exercise regimen will result in an increase of ~5 points in the physical function subscale of the SF-36 whereas the usual medical care group will result in an overall loss of ~3 points over 3 months. Therefore, we anticipate a difference between the exercise and usual medical care groups of ~8 points in change of the physical function subscale from baseline to 3 months. A priori, 36 subjects per group will be required to achieve 80% power at an alpha level of 0.05 (two-tailed), and to demonstrate a difference between groups at the end of the 3-month intervention. Therefore, to adequately ensure that we have sufficient subject numbers at the end of the intervention (accounting for a drop-out rate of ~20%), 90 subjects will be randomized in a ratio of 1:1 to exercise and usual medical care groups, respectively.

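### The named repeated measures ANOVA keeps only men with complete data at every modelled visit, which sits poorly with intention-to-treat and can discard valid 3-month primary values

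*Protocol article*

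**What the plan says.** The Statistical analysis section of the protocol article states that "an intention-to-treat approach will be applied" and that SPSS will be used. It lists descriptive statistics, t tests, correlation and regression, and a two-way (group by time) "repeated measures ANOVA (or ANCOVA as appropriate) to examine differences between groups over time". It does not say which of these is the primary test or which visits enter the model, and it states no rule for men with a missing visit.

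The Measurements section sets visits at baseline, 3 months and 6 months. The Calculation of sample size section places the powered comparison at 3 months ("to demonstrate a difference between groups at the end of the 3-month intervention"). It sets recruitment so as to have "sufficient subject numbers at the end of the intervention (accounting for a drop-out rate of ~20"%), so the allowance covers loss up to month 3. The opening of Methods/Design and Table 1 have usual-care men offered or receiving the exercise programme between months 3 and 6.

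**The concern.** Intention-to-treat means that men are analysed as randomised, whatever happens to them later. Classical repeated measures ANOVA needs a value at each time level in the model and leaves out any man who lacks one. On the plan's own drop-out figure that is about 18 of 90 men (0.20 × 90), before any loss after month 3.

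The second effect is specific to this design. With three visits modelled, absence at month 6 also removes a value already recorded at month 3, the visit that answers the primary question. Nothing is gained in return: the 6-month value is not needed for the 3-month contrast, and by then usual-care men may be exercising too.

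In men with metastatic disease, whether a man returns may well depend on how he has fared. A completer estimate presented as intention-to-treat would then be biased by an unknown amount, and power would be lost without need.

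**Working it through.** **Inputs**, all from Calculation of sample size: SD of change ("equates to ~12 points following a 3-month intervention"), expected difference ("8 points in change of the physical function subscale from baseline to 3 months"), "36 subjects per group will be required to achieve 80% power at an alpha level of 0.05 (two-tailed"), 45 randomised per arm, and about 20% drop-out.

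**Step 1. Reproduce the plan.**
- n per arm = 2 × (1.960 + 0.842)² × 12² / 8² = 2 × 7.85 × 2.25 = 35.3, so 36.
- Inflation: 36 / 0.80 = 45 per arm, 90 in total. Both stated figures reproduce.

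**Step 2. Power when only complete men are analysed.** The noncentrality is 8 / (12 × √(2/n)). Power is from the noncentral t distribution, with the normal approximation beside it.

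| Total incomplete | Men per arm | Noncentrality | Power (t) | Power (normal) |
|---|---|---|---|---|
| 0% | 45 | 3.162 | 87.9% | 88.5% |
| 20% (the plan's allowance) | 36 | 2.828 | 79.7% | 80.7% |
| 25% (assumed) | 33.75 | 2.739 | 77.0% | 78.2% |
| 30% (assumed) | 31.5 | 2.646 | 74.0% | 75.4% |

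At the planned rate, complete-case analysis leaves exactly the 36 men that were powered for. The allowance refers to month 3, so loss between months 3 and 6 is unbudgeted only if month 6 is in the model. A total of 25% would need 2.25 of the 36 to be lost in that interval (6.25%); a total of 30% would need 4.5 of 36 (12.5%). The article gives no rate for that interval.

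**Step 3. Direction of bias.** The article gives nothing from which to estimate this, so the following is illustrative. Take 3-month changes as normal with means +5 (exercise) and −3 (usual care) and SD 12. Let the log-odds of loss rise by 0.02 to 0.08 for each point of poorer change, which multiplies the odds by exp(12 × 0.02) = 1.3 to exp(12 × 0.08) = 2.6 per SD. Set loss at 15%.
- Selective loss in the exercise arm only: the difference is overstated by about 0.4 to 1.5 points.
- The same selection in both arms, relative to each arm's own mean: bias is about 0.
- The same selection in both arms on absolute change (15% loss overall): the difference is understated by about 0.1 to 0.7 points, because more of the poorly faring men are in usual care.

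Set against the expected 8 points, the sign and size depend wholly on who leaves.

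**The case against.** The strongest reply is that the article never commits to a three-visit ANOVA for the primary test. A t test on change, an ANOVA on months 0 and 3, or an ANCOVA at 3 months would all keep a man who misses month 6. It also states no deletion rule: imputation before the ANOVA would fit the text, and the method for missing data may sit in an analysis plan that is not shown. This stands in part. It makes the matter a tension rather than a contradiction, and the silence on missing data is not itself the point. It does not remove the point, because the only method named for differences over time does not by itself deliver the principle named beside it. The phrase allowing ANCOVA leaves the choice open, and a 3-month ANCOVA still omits men with no 3-month value.

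Three stronger readings are tempting and are not supported:
- **That the ANOVA takes the trial below 80% power.** The inflation from 36 to 45 already pays for 20% loss. Lower figures need loss that the article does not state.
- **That the benefit of exercise will be overstated.** If poorly faring men leave both arms, the bias is near zero or reversed.
- **That men who stop exercising become missing data.** The Safety of the exercise program section has men with bone pain cease the programme; it does not end their assessments. Nor is later access to the programme a sure incentive for usual-care men to stay, since the text of Methods/Design makes it conditional on the intervention being judged feasible and efficacious.

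It is also fair to say that a mixed model cannot recover men with no value after baseline. Its main gain is the men seen at one follow-up visit but not the other.

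**Conclusion.** The point holds in a limited form. As worded, the plan pairs intention-to-treat with a method that in its classical form gives a completer estimate, and with three visits modelled it can discard valid 3-month primary values. The likely harm is bias of unknown sign; the sizes in Step 3 rest on assumed loss rates and selection slopes. Power stays at its stated level at the planned 20% loss (79.7%) and slips to about 77% or 74% only if total incompleteness reaches an assumed 25% or 30%. This should be settled before analysis because the remedy is nearly free, not because the sample size is wrong.

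**What to change.** In the Statistical analysis section, replace repeated measures ANOVA with a likelihood-based mixed model for repeated measures (available as MIXED in SPSS), with these features:
- terms for group, visit and their interaction, with the baseline value and the chemotherapy stratum included;
- unstructured covariance across visits;
- all available values from every randomised man, analysed in the arm to which he was allocated;
- the between-group contrast at 3 months named as the primary test.

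Add one sensitivity analysis for non-random loss, for example giving exercise-arm drop-outs the usual-care trajectory to month 3. This also addresses men with no follow-up value, whom the mixed model cannot recover. In Calculation of sample size, state that the 80% power refers to 36 men per arm evaluable at 3 months.

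The cost is a few sentences and a little extra programming in the software already chosen. Recruitment, visits and sample size do not change.

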### Randomisation

Patients will be randomly allocated in a ratio of 1:1 to the two study arms for the experimental M3EP exercise intervention or usual medical care groups, subject to maintaining approximate balance regarding stratification for current chemotherapy (yes/no). A research methods consultant with no patient contact will be responsible for randomisation. The exercise physiologists and other researchers conducting the study measures will be blinded to a given participant's group allocation. The exercise intervention will be provided by exercise physiologists not in the research team or performing the tests.

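### The primary analysis is not committed to adjusting for the baseline score or the chemotherapy stratum; a named ANCOVA would add some power to a valid 80% design using data the trial already needs

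*Protocol article*

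**What the plan says.** Three sections of the protocol article bear on this point.

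- **Calculation of sample size.** The target is a "difference between the exercise and usual medical care groups of ~8 points in change of the physical function subscale" over the first 3 months. The SD of that change "equates to ~12 points following a 3-month intervention". The section concludes that "36 subjects per group will be required to achieve 80% power at an alpha level of 0.05 (two-tailed"). It adds an allowance for drop-out of about 20% and arrives at 90 randomised.
- **Randomisation.** Allocation is 1:1, "subject to maintaining approximate balance regarding stratification for current chemotherapy (yes/no").
- **Statistical analysis.** "Analyses will include standard descriptive statistics, Student's t tests, correlation and regression". The same sentence goes on to two-way (group by time) repeated measures ANOVA and allows ANCOVA in its place where suitable. The section does not say which method answers the primary question, what would trigger ANCOVA, or which covariates would enter. Neither the baseline score nor current chemotherapy appears as a model term.

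**The concern.** The methods stated without condition, t tests and repeated measures ANOVA, are unadjusted. Restricted to baseline and 3 months, the group by time test is the same test as a t test on change scores. It uses the baseline by subtraction, which fixes its coefficient at 1, whereas ANCOVA estimates that coefficient and so leaves a residual variance that is no larger and usually smaller. A change-score comparison also carries more of any chance baseline difference between arms into the estimate, although it is unbiased over repeated randomisations.

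The stratum raises a related point. Balancing the arms on chemotherapy removes a source of variation from the difference between arms. A test that leaves the factor out still counts that variation in its standard error, so the interval is somewhat too wide.

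What is at stake is precision in a trial planned at 80% power with no stated reserve beyond drop-out. An analysis chosen in advance also spares the trial any question about why one listed test was preferred over another.

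**Working it through.** **Inputs from the article (Calculation of sample size):** difference in change 8 points (+5 against −3), SD of change 12, two-sided alpha 0.05, power 80%, 36 evaluable per arm, drop-out about 20%.

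**Inputs not in the documents, taken as assumptions:** the correlation rho between baseline and 3-month scores (range 0.5 to 0.9), the ratio k of the 3-month SD to the baseline SD (k = 1 unless stated), and the share R² of change-score variance explained by chemotherapy (5% and 10%).

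**1. The plan's own figure.** n per arm = 2 × (1.960 + 0.842)² × 12² / 8² = 35.3, rounded up to 36. Then 36 / 0.80 = 45 per arm, or 90 in total. Both figures reproduce, so the sample size takes no credit for covariate adjustment. Power at 36 per arm is 79.7% by the noncentral t and 80.7% by the normal approximation.

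**2. Adjusting for baseline, equal SDs.** With a common SD s at each visit, Var(change) = 2s²(1 − rho) and the ANCOVA residual variance is s²(1 − rho²). Their ratio is (1 + rho)/2, so the residual SD is 12 × √((1 + rho)/2). Power is by the noncentral t with 69 degrees of freedom. The half-width of the 95% CI is 1.96 × SD × √(2/36).

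| Analysis | Variance ratio | SD | Power at 36 per arm | CI half-width (points) |
|---|---|---|---|---|
| Change score | 1 | 12.0 | 79.7% | 5.5 |
| ANCOVA, rho 0.5 | 0.75 | 10.4 | 89.6% | 4.8 |
| ANCOVA, rho 0.6 | 0.80 | 10.7 | 87.7% | 5.0 |
| ANCOVA, rho 0.7 | 0.85 | 11.1 | 85.7% | 5.1 |
| ANCOVA, rho 0.8 | 0.90 | 11.4 | 83.6% | 5.3 |
| ANCOVA, rho 0.9 | 0.95 | 11.7 | 81.6% | 5.4 |

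**3. Adjusting for baseline, unequal SDs.** In units of the baseline variance, Var(change) = 1 + k² − 2·rho·k and the ANCOVA residual variance is k²(1 − rho²). Their difference is (1 − rho·k)², which is never negative and is zero when rho·k = 1.

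- rho 0.7, k 1.2: 0.734 / 0.760 = 0.97, against 0.85 with equal SDs.
- rho 0.8, k 1.25: 0.5625 / 0.5625 = 1, so there is no gain.

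**4. Omitting the stratum.** With near-exact balance on chemotherapy, the true standard error of the unadjusted difference is the nominal one times √(1 − R²). The nominal value is 12 × √(2/36) = 2.83, so the standardised effect is 8 / 2.83 = 2.83. By the normal approximation, the actual alpha is 2 × [1 − Φ(1.96 / √(1 − R²))]. Unadjusted power is Φ((2.83 − 1.96) / √(1 − R²)), and adjusted power is Φ(2.83 / √(1 − R²) − 1.96).

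| R² | Actual alpha, stratum omitted | Power, omitted | Power, included | Cost of omission |
|---|---|---|---|---|
| 5% | 0.044 | 81.4% | 82.7% | 1.3 points |
| 10% | 0.039 | 82.0% | 84.6% | 2.6 points |

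This step adjusts the change score for chemotherapy alone. Its gain should not simply be added to that in step 2, because the baseline score may already carry part of the chemotherapy effect.

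**The case against.** The strongest objection is one of scope. This is a condensed article whose analysis plan is not shown, and a covariate list is commonly left to that plan, so its absence is no error in itself. That stands. But the section is not merely silent. It sets out unadjusted methods and makes ANCOVA conditional without giving the condition, and that wording can be improved where it is.

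Several stronger readings are tempting and are not supported.

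- *A reader might infer that the analysis ignores the stratification factor.* Regression and ANCOVA are both listed, and either could carry it. The text does not commit to using the factor, nor does it exclude it.
- *A reader might infer that precision is already lost.* It is lost only if an unadjusted method is used for the primary question. Even then, the change-score comparison is unbiased under randomisation and delivers the planned power.
- *A reader might infer that ANCOVA gains appreciably whenever the correlation is below 1.* Step 3 shows that this needs an assumption about the two SDs, which the article does not give.
- *A reader might argue that the SD will exceed 12 in men with bone metastases, so the extra power is needed.* The Background says that the team's recent trial excluded such men, but no document gives another SD. That would be a question about the sample-size input.
- *A reader might equate the planned ANOVA with the change-score t test.* That holds for two visits. Measurements are scheduled at 0, 3 and 6 months, and the article does not say which visits enter the model.
- *A reader might infer inflated false positives from omitting the stratum.* The effect runs the other way: the test becomes slightly conservative.

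**Conclusion.** The point holds as a modest improvement in efficiency and clarity. It does not show an invalid analysis or an undersized trial. The stated sample size is correct for the unadjusted change-score comparison, which has about 80% power at 36 per arm.

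Committing to adjustment for the baseline score would raise power by about 10 points at a correlation of 0.5 and about 2 points at 0.9, with equal SDs at the two visits. The gain falls towards zero as the product of the correlation and the SD ratio approaches 1. Including the chemotherapy stratum would recover perhaps 1 to 3 points if chemotherapy explains 5 to 10% of the variance. The correlation, the SD ratio and the variance share are all assumptions.

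**What to change.** Replace the open list, for the primary question, with one named analysis: an ANCOVA of the 3-month SF-36 physical function score on arm, baseline score and current chemotherapy (yes/no), reporting the adjusted difference between arms with its 95% CI. State that t tests and repeated measures ANOVA are supportive, and remove the conditional wording about ANCOVA. Use the same form for the continuous secondary endpoints, each with its own baseline value.

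The cost is a sentence or two in the analysis section or the analysis plan, written before outcome data are seen. No new data are needed: the baseline score is already scheduled and chemotherapy status must be known to randomise. The sample size can stay at 90, with any gain kept as reserve.

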## Methods/Design

This is a two-armed prospective randomized controlled trial that will examine the efficacy and safety of a modular multi-modal physical exercise program in prostate cancer survivors with bone metastases. The trial will be a multisite study with clinical sites in Western Australia and New South Wales. Participants randomly assigned to the M3EP exercise intervention group will receive a 3-month supervised exercise intervention program (based on bone lesion location/extent) (Table 1). Participants in the usual medical care group will be asked not to change their baseline levels of physical activity and will be offered the same exercise program after the 3-month control period if the intervention is deemed to be feasible and efficacious.

**Table 1 T1:** Summary of study design

Months	0			3			6
**Exercise **(M3EP)		Intervention (n = 45)			Follow-up from 3-6 month		

**Usual Medical Care**		Usual Care (n = 45)			**Usual Medical Care **to receive same intervention (M3EP) from 3-6 month		

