### Measurements

Measurements for primary and secondary endpoints will take place at baseline, 3 months (end of the intervention) and 6 months follow-up.

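### The planned group × time ANOVA is not restricted to the powered baseline-to-3-month contrast, and month 6, when usual care is due to exercise, could enter the efficacy test

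*Protocol article*

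**What the plan says.** All references are to the protocol article.

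- **Calculation of sample size.** The primary outcome is the SF-36 physical function subscale. The SD of its change "equates to ~12 points following a 3-month intervention". The exercise program "will result in an increase of ~5 points in the physical function subscale of the SF-36", while "the usual medical care group will result in an overall loss of ~3 points over 3 months", so the target is "8 points in change of the physical function subscale from baseline to 3 months". The stated purpose is to "demonstrate a difference between groups at the end of the 3-month intervention".
- **Measurements.** "Measurements for primary and secondary endpoints will take place at baseline, 3 months (end of the intervention) and 6 months follow-up".
- **Methods/Design, Table 1.** The usual care arm is "to receive same intervention (M3EP) from 3-6 month". The paragraph above the table instead describes an offer, made only if the program has been judged workable and effective.
- **Statistical analysis.** Differences between groups are assigned to "two-way (group × time) repeated measures ANOVA (or ANCOVA as appropriate) to examine differences between groups over time". The same sentence also lists t tests, correlation and regression, without giving them a role. It does not say which visits enter the ANOVA, which contrast is read, or which test is primary.

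**The concern.** The powered question concerns two visits, baseline and month 3. The method tied to group differences is worded for differences over time, and the primary endpoint is collected at three visits. The natural reading is therefore a three-visit ANOVA.

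Under Table 1, the third visit compares men who exercised first and were then followed up with men who exercised later. That is not exercise versus usual care. An interaction test with 2 degrees of freedom asks whether the between-arm difference changes across any of the visits. A significant result would not show a 3-month benefit, and a non-significant one would not be the outcome of the test for which the trial was sized. The primary efficacy conclusion is at stake, as are the secondary endpoints measured on the same schedule.

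**Working it through.** **Inputs from the sample size section:** difference in change 8 points (+5 against −3), SD of change 12, two-sided alpha 0.05, 36 evaluable per arm, about 20% dropout.

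**Inputs not in the article, so assumed:** the between-arm difference at month 6 (called d6) and the correlation between visits. Both are varied below.

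**1. The plan's own figure.** n per arm = 2 × (1.960 + 0.842)² × 12² / 8² = 35.3, rounded up to 36. Power at 36 per arm is 80.7% by the normal approximation and 79.7% by the noncentral t. Dropout: 36 / 0.80 = 45 per arm, 90 in total. The stated figures reproduce.

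**2. Group × time with baseline and month 3 only.** An SD of change of 12 implies a within-subject error variance of 12² / 2 = 72. The noncentrality is

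λ = (n / 2) × Σ(d_t − mean d)² / 72.

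For differences (0, 8) the sum of squares is 16 + 16 = 32, so λ = 18 × 32 / 72 = 8.0. With F(1, 70), power is 79.7%. This is the t test on change, and it matches the plan.

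**3. Group × time with all three visits, equal correlation, F(2, 140).** Suppose the exercise arm goes 0, +5, +5, and the controls go 0, −3, +2 because they gain the same 5 points once they start. The differences are (0, 8, 3), with mean 3.67 and sum of squares 32.67. Then λ = 18 × 32.67 / 72 = 8.17 and power is 71.7%. Varying d6:

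| Month-6 difference d6 | λ | Power |
|---|---|---|
| 0 (full catch-up) | 10.67 | 83.3% |
| 1 | 9.50 | 78.5% |
| 2 | 8.67 | 74.4% |
| 3 | 8.17 | 71.7% |
| 4 | 8.00 | 70.8% |
| 6 | 8.67 | 74.4% |
| 8 (no catch-up) | 10.67 | 83.3% |

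**4. Unequal correlation.** This uses first-order autoregressive correlation of 0.5 to 0.8 between adjacent visits, the 3-month change SD kept at 12, a Greenhouse-Geisser correction and 20,000 simulated trials per case. Power is 80% to 77% at d6 = 0, 63% to 58% at d6 = 4, and 73% to 67% at d6 = 8.

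**5. Significance without a 3-month effect.** For differences (0, 0, −8), the sum of squares is 42.67 and λ = 10.67, so the interaction is significant in 83.3% of trials under equal correlation. This extreme case shows only that the test can respond to months 3 to 6 alone. It is not a forecast.

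**The case against.** The strongest reply is that the article never says that month 6 enters the primary test. Measuring at a visit does not put it into the analysis. A two-visit group × time ANOVA fits the wording too, as would a t test on 3-month change, and t tests and ANCOVA are named in the same sentence. The sample size section gives both the contrast and its time point, and the remaining model detail could sit in an analysis plan that is not shown.

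Much of this stands. Use of month 6 is the natural reading, not an explicit statement, and the ANOVA is not the only method listed. But the article does more than leave a detail open. It ties group differences to a method and collects the endpoint at three visits, and nothing restricts that method to the two visits used for the sample size.

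Two further objections also stand in part:

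- The delayed program is conditional in the Methods/Design text, so it is not certain that every control will have exercised by month 6. Table 1 carries no such condition. If the text governs, what month 6 means depends on how the program is judged after the control period, which does not make it a better visit for an efficacy test.
- The case in step 5 fits poorly with that condition, because a program showing no 3-month benefit would hardly be judged effective and offered. It carries little weight.

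**Conclusion.** The point holds as a mismatch between the powered question and an analysis method that is not restricted to it. If all three visits are used, the omnibus interaction answers a different question. Its power at 36 per arm under equal correlation is about 71% to 83% for month-6 differences of 0 to 8 points, and 72% if controls gain the same 5 points. It falls as low as 58% under the autoregressive patterns tried. The baseline-to-3-month contrast has the stated 80%. The three-visit figures rest on assumed month-6 differences and correlations.

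Three stronger readings are not supported:

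- **That the trial loses its 80% power.** A reader might infer this, but the three-visit interaction reaches 83.3% at a month-6 difference of 0 or of 8 under equal correlation.
- **That control catch-up always dilutes the test.** For the interaction this is not generally true, because a difference that rises and then falls is itself an interaction.
- **That efficacy will be judged on the group main effect averaged over visits.** Its power would be much lower: 35%, 27% and 20% at correlations of 0.5, 0.6 and 0.7 for differences (0, 8, 3). But nothing in the article makes it the efficacy test, and part of the loss comes from averaging in baseline.

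**What to change.** - Name one primary test: the between-arm difference in SF-36 physical function at 3 months, adjusted for baseline. Either an ANCOVA or the month-3 contrast of a longitudinal model will do.
- Use the same 3-month contrast for the secondary efficacy endpoints.
- Report month 6 separately, as maintenance within the exercise arm and as change from month 3 to month 6 within the delayed arm. Label any between-arm comparison at month 6 as immediate versus delayed exercise, not as exercise versus usual care.
- Reconcile Table 1 with the Methods/Design text on whether the later program for the usual care arm is conditional, so that the month-6 data can be described correctly.

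This takes about a paragraph of wording, with no new patients or data. The cost is giving up the three-visit omnibus p-value as evidence of efficacy.
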